**TABLE 2: Risk of LBW among 211,318 singleton infants born to women of known HIV status in Lusaka**

|                    | <2500 gms* |                   | <2000 gms |                   | <1500 gms |                   |
|--------------------|------------|-------------------|-----------|-------------------|-----------|-------------------|
|                    | N          | %                 | N         | %                 | N         | %                 |
| HIV - (78%) | 19828      | 11.8              | 7081      | 4.2               | 3878      | 2.3               |
| HIV + (22%) | 7956       | 17.2              | 3088      | 6.7               | 1720      | 3.7               |
| RR (95%CI)  |            | 1.46 (1.43, 1.50) |           | 1.59 (1.52, 1.65) |           | 1.61 (1.53, 1.71) |

\*NB: Birth weight categories are not mutually exclusive

- Although low birth weight is not a perfect proxy for prematurity (most notably, it does not distinguish growth restriction from preterm birth), it is the only outcome we have to estimate the preterm birth rates in HIV+ versus HIV- women in our setting. We used the antenatal HIV prevalence and relative risk of LBW delivery from TABLE 2, to estimate a rate of prematurity in HIV-infected women that would correspond to an overall rate of 15.5% (Goal Seek Function, MS Excel).
- Under these assumptions, we estimate that the prematurity rate would have to be **20.9%** among HIV-infected women and 14.0% among HIV-uninfected women to produce an overall rate of 15.5% in a setting of 22% maternal HIV prevalence at UTH. To be conservative, we have not assumed any additional prematurity risk conferred by receipt of ART.
- Finally, a study of more than 100,000 public sector deliveries performed by our group found a stillbirth rate of 21 per 1,000 live births. Among the 21,816 HIV-infected parturients, the stillbirth rate was 27 per 1000 (95% CI: 25, 29). Because our composite primary outcome includes stillbirth, we add a 2.7% stillbirth rate to the 20.9% prematurity rate to arrive at a baseline event rate of 23.6%. Rounding to 2 significant figures, we have set the baseline event rate, **p1 = 0.24**.

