### **7.9.2 Sample size calculation: baseline event rate (p1)**

We estimated the baseline rate of our primary outcome as follows:

- The ZEPRS system in Lusaka estimates GA at birth from the last menstrual period (LMP), a method that, in our setting, consistently overestimates prematurity. A study performed by our group of all public sector births in Lusaka between 2006 and 2010 found that 31,896 of 100,408 women (31.7%) delivered before their LMP-derived EGA reached 37 weeks completed gestation.
- As of April 2017, 1116 women had been enrolled in the GAPPS Preventing Preterm Birth study and 497 had delivered. All enrollees have an early dating ultrasound at 20-24 weeks. Based on reliable GA estimates from these ultrasounds, 18.1% of women overall delivered prior to 37 weeks.
- A large international modeling effort published by *Blencowe et al* in 2010 estimated that 12.9% of infants in Zambia are born prior to 37 weeks of gestation. While this

effort aggregated hundreds of published studies to inform its models, no data were included from Zambia. Since the Zambia estimate is not consistent with our own measurements, we believe it may be artificially lowered by inclusion of country economic data in the models. (Zambia is categorized as “lower-middle income” economy, a threshold it achieves only by a tiny margin; data from neighboring Zimbabwe are consistently reported in the 17-20% range.)

- Given the suspected underestimation of gestational age in the ZEPRS data, and the relatively small sample size in the GAPPS cohort, we applied the *Blencowe* figures to existing data from our site for these sample size calculations, arriving at an overall prematurity rate of 15.5% (arithmetic mean of Zambia country estimates and current PTB rate in GAPPS) for our calculation of the baseline event rate. We note that to underestimate the prematurity rate would be conservative vis-à-vis our sample size calculations.

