- Available estimates for Zambia do not disaggregate prematurity risk by HIV status. We therefore queried ZEPRS, which does capture birth weight completely and correctly. We used birth weight as a proxy for prematurity to estimate the relative risk of preterm birth by HIV status in our setting. An analysis of 211,318 public sector singleton births in Lusaka between 2006 and 2013 found that 17.2% of HIV-exposed infants weighed <2500g at delivery, compared to 11.8% unexposed infants. (Chibwesha et al, submitted for publication; TABLE 2).

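### The 20.9% preterm rate in HIV-infected women does not follow from the Table 2 inputs named in section 7.9.2; those inputs give about 20.5-20.6%, so p1 rounds to 0.23 rather than 0.24

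*Protocol*

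**What the plan says.** Section 7.9.2 builds p1 in four steps.

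- It averages two estimates of preterm birth, 12.9% and 18.1%, "arriving at an overall prematurity rate of 15.5" per cent.
- It takes low birth weight as a proxy for prematurity, reporting that "17.2% of HIV-exposed infants weighed <2500g at delivery, compared to 11.8% unexposed infants". Table 2 gives the matching relative risk and interval as "1.46 (1.43, 1.50").
- It then splits the overall rate by HIV status: "We used the antenatal HIV prevalence and relative risk of LBW delivery from TABLE 2, to estimate a rate of prematurity in HIV-infected women". The reported answer is 20.9% "among HIV-infected women and 14.0% among HIV-uninfected women to produce an overall rate of 15.5" per cent, "in a setting of 22% maternal HIV prevalence at UTH".
- It adds a stillbirth rate of 2.7% to reach 23.6%. "Rounding to 2 significant figures, we have set the baseline event rate" at 0.24.

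Section 7.9.4 carries 24% forward, applies a 38% reduction to reach 15%, and states 80% power with 325 per arm (two-sided Fisher's exact test, 0.05). It enrols 400 per arm to allow for 15% loss and for uncertainty in p1 and in efficacy.

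**The concern.** The two printed rates should stand in the ratio of the relative risk used to split them. Their ratio is 20.9/14.0 = 1.49, while Table 2 gives 1.46. A reader who repeats the stated derivation therefore gets a different rate in infected women and, after the stillbirth add-on and the stated rounding, a different p1.

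p1 is the base of the sample size. The error also runs in the optimistic direction: a higher control rate at a fixed relative reduction gives more power. The section elsewhere describes its choices as conservative.

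**Working it through.** **Inputs.** Overall preterm rate 15.5%, HIV prevalence 22%, stillbirth add-on 2.7% (all section 7.9.2); relative risk 1.46 (Table 2, under 2500 g; unrounded 17.2/11.8 = 1.4576).

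**Formula.** Let x be the rate in uninfected women, v the prevalence and RR the relative risk. Then overall = (1 − v)·x + v·RR·x, so x = overall / (1 − v + v·RR), and the rate in infected women is RR·x.

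**With the named inputs.** x = 15.5 / (0.78 + 0.22 × 1.46) = 15.5 / 1.1012 = 14.08%. Infected: 1.46 × 14.08 = 20.55%. Total: 20.55 + 2.7 = 23.25%, which is 0.23 to two significant figures.

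**What reproduces the printed figures.**

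| RR | Uninfected | Infected | Plus 2.7% |
|---|---|---|---|
| 1.4576 (17.2/11.8) | 14.08% | 20.53% | 23.23% |
| 1.46 (Table 2, <2500 g) | 14.08% | 20.55% | 23.25% |
| 1.49 | 13.99% | 20.85% | 23.55% |
| 1.50 | 13.96% | 20.95% | 23.65% |
| 1.59 (Table 2, <2000 g) | 13.72% | 21.81% | 24.51% |
| 1.61 (Table 2, <1500 g) | 13.67% | 22.00% | 24.70% |
| Printed | 14.0% | 20.9% | 23.6% |

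An infected rate of exactly 20.9% needs RR ≈ 1.495. At RR = 1.50 the unrounded result is 20.946%, which displays as 20.9%. No point estimate in Table 2 gives the printed pair.

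**Input rounding.** Letting the overall rate run over 15.45-15.55%, prevalence over 21.5-22.5% and RR over 1.455-1.465, the infected rate stays within 20.4-20.7% and the total within 23.1-23.4%. It never reaches 20.9%, and p1 always rounds to 0.23.

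**Power** (exact power of the two-sided Fisher test at 0.05). The plan's own claim is reproduced first. The 340 column is 400 × 0.85. The corrected control rates keep the 38% reduction: 23.25% × 0.62 = 14.4%, and 0.23 × 0.62 = 0.1426.

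| Control v active | Power at 325/arm | Power at 340/arm | n/arm for 80% |
|---|---|---|---|
| 24% v 15% (section 7.9.4) | 80.4% | 82.2% | plan states 325 |
| 23.25% v 14.4% (unrounded) | 79.9% | 81.7% | 326 |
| 0.23 v 0.1426 (p1 rounded) | 79.4% | 81.2% | 331 |

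Against the plan's 82.2% at 340 per arm, the loss is about 0.4 to 1.0 percentage points, depending on the rounding basis.

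**The case against.** The strongest reply is that nothing in the design turns on this. A shift of about 0.35 percentage points (20.9 − 20.55) is far smaller than the other uncertainty in the section, where the 15.5% is itself the midpoint of 12.9% and 18.1% and low birth weight is an admittedly imperfect proxy. Section 7.9.4 enlarges the trial partly because p1 is uncertain. Unrounded, 325 per arm still gives 79.9%. Rounding the active-arm rate up from 14.88% (24% × 0.62) to 15% also costs some power and partly offsets the rounding of p1. All of this stands and limits the size of the point. It does not make the printed figures follow from the named inputs.

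Three stronger readings are tempting, and the documents do not support them:

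- **That the relative risk was taken from the meta-analysis in section 4.2.** That section does give 1.50, but 1.50 is also the upper confidence limit in Table 2, and 1.46 may simply have been rounded. The protocol does not say which.
- **That the trial needs 331 evaluable women per arm.** This holds only if 23.25% is first rounded down to 0.23; without rounding, 326 suffice.
- **That power falls to about 70%.** That comes from applying the 0.62 only to the preterm component, which is a separate question. Doing so with the protocol's own 20.9% (23.6% v 20.9% × 0.62 + 2.7% = 15.7%) already gives about 71% at 340 per arm. The present correction accounts for only about one point of it.

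**Conclusion.** The printed 20.9% and 14.0% are inconsistent with the method and inputs that section 7.9.2 declares. Those inputs give about 20.5-20.6% and 14.1%, a total of 23.2-23.3%, and p1 = 0.23 under the plan's own rounding rule.

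This takes the Table 2 relative risk to be the under-2500 g value. That is the only contrast quoted in the text, and the other two columns miss the printed pair by more. The power figures assume that the 38% reduction applies to the whole composite, as section 7.9.4 does, and that 15% of women are lost.

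On that basis the cost is about half a point to one point of power at 340 evaluable per arm, which remains above 80%. The planned 400 per arm is not called into question. What needs correcting is a stated design figure and its derivation.

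**What to change.** Take one of two routes.

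1. **Keep Table 2 as the source.** Change section 7.9.2 to 20.6% in infected and 14.1% in uninfected women, with p1 = 23.3% (0.23 to two significant figures). Change section 7.9.4 to an active-arm rate of 14.4% under the 38% reduction. Restate power on a single rounding basis. Unrounded, this is 79.9% at 325 per arm, 326 per arm for 80%, and about 81.7% at 340. With p1 = 0.23 and p2 = 0.1426, it is 79.4%, 331 and 81.2%. Do not mix the two, for example 23.3% with 14.3%.
2. **Keep 20.9% and 14.0%.** State that a relative risk of about 1.50 was used, give its source, and remove the statement that the Table 2 estimate was the input.

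Either is a text correction. Route 1 leaves a slightly less favourable power statement. Enrolment stays at 400 per arm.

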### 7.9.3 Sample size calculation: effect size

A 2013 meta-analysis estimated the RR of preterm delivery for women using *any* progestogen to be 0.55 (95%CI: 0.42, 0.74). For the purposes of our study, we will use the more conservative subtotal estimate from only the IM studies (FIGURE 1). This 0.62 RR translates to a **38% relative efficacy**.

**FIGURE 1: Summary of IM progesterone trials in Cochrane meta-analysis**

| Study or subgroup                                                                        | Progesterone
n/N | Placebo
n/N |
|------------------------------------------------------------------------------------------|---------------------|----------------|
| I Intramuscular                                                                          |                     |                |
| Ibrahim 2010                                                                             | 8/25                | 13/25          |
| Johnson 1975                                                                             | 2/18                | 12/25          |
| Meis 2003                                                                                | 111/306             | 84/153         |
| Saghafi 2011a                                                                            | 16/50               | 30/50          |
| Subtotal (95% CI)                                                                 | 399          | 253     |
| Total events: 137 (Progesterone), 139 (Placebo)                                          |                     |                |
| Heterogeneity: $\tau^2 = 0.0$ ; $\chi^2 = 2.84$ , $df = 3$ ( $P = 0.42$ ); $I^2 = 0.0\%$ |                     |                |
| Test for overall effect: $Z = 5.11$ ( $P < 0.00001$ )                                    |                     |                |

**Figure 2: Sample size per arm for 80% power**

[figure not shown]

### 7.9.4 Trial sample size

In summary, we postulate that 17P will reduce the proportion of HIV-infected women experiencing the composite endpoint by 38% (from 24% to 15%). We used SAS 9.3 (SAS, Cary, NC) to determine that a trial with 325 patients per arm would have 80% power to detect this effect size (based on a 2-sided Fisher's exact test at the 0.05 significance level; FIGURE 2). To **allow for up to 15% follow-up loss** (although prior experience from our sites suggests it will be half this) and to account for uncertainty in our estimates of baseline event probability (p1) and relative efficacy of the intervention, we plan to enroll **400 women per arm** in the trial. As FIGURE 2 indicates, the study will have 80% power to demonstrate any combination of baseline event rate and relative efficacy that falls below the red horizontal line (after accounting for follow-up losses and any missing outcomes).

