#### **4.5.2 Human Studies**

Several controlled clinical trials and epidemiological studies have demonstrated the safety of 17P in human pregnancy. In randomized trials of 17P for the prevention of PTB, no significant risk of adverse birth outcomes has been noted in women with progesterone exposure compared to placebo. While some trials have reported a statistically non-significant increased risk of stillbirth and/or miscarriage, others show no trend, and others report a nonsignificant reduction in stillbirth with 17P. A individual participant data meta-analysis of 13 trials including 3,768 women showed a relative risk of adverse perinatal outcome of 1.1 (95% CI 0.97–1.4) among women receiving 17P compared to placebo, and concluded that treatment with 17P does not have an effect on adverse perinatal outcomes.

Two extensive reviews argue that no evidence exists that exposure to 17P in utero induces genital malformations in female fetuses. In addition, the rates of non-genital malformations in fetuses exposed to 17P compared to unexposed fetuses have been similar in numerous large clinical trials and population reports. In one, 988 infants exposed to exogenous progesterone or 17P were compared to a matched cohort of unexposed infants in the United States; similar rates of all congenital malformations were reported between the two cohorts. A prospective study comparing 1,608 newborns exposed to progestogens (either oral medroxyprogesterone caproate or 17P, or both) in the first trimester of pregnancy and 1,146 unexposed newborns found nearly equal rates of both major and all malformations between the two groups.

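### The sample size applies a risk ratio estimated for birth before 37 weeks to a composite that includes added stillbirths; without that step, power is about 71–76% at the 15% loss allowance and 75–80% at the expected loss

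*Protocol*

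**What the plan says.** The primary outcome is live birth before 37 weeks or stillbirth at any gestational age (sections 6.1 and 7.9.1). The control rate is built in section 7.9.2: "we add a 2.7% stillbirth rate to the 20.9% prematurity rate to arrive at a baseline event rate of 23.6" percent, then rounded to 24%. The 20.9% derives from an overall rate of 15.5%, the mean of a 12.9% model estimate and a local cohort figure in which "18.1% of women overall delivered prior to 37 weeks".

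The effect size comes from section 7.9.3, where a meta-analysis "estimated the RR of preterm delivery for women using" any progestogen. The subtotal for intramuscular trials is used: "This 0.62 RR translates to a" 38% relative efficacy. Section 4.3 confirms that the pooled outcome was birth before 37 weeks.

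Section 7.9.4 combines the two: "we postulate that 17P will reduce the proportion of HIV-infected women experiencing the composite endpoint by 38% (from 24% to 15" percent). It concludes that "a trial with 325 patients per arm would have 80% power to detect this effect size". The sizing rests on Fisher's exact test, two-sided at 0.05. It enrols 400 per arm to cover loss of up to 15% and uncertainty in the baseline rate and efficacy, and expects about half that loss.

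On stillbirth, section 4.5.2 says that "some trials have reported a statistically non-significant increased risk of stillbirth and/or miscarriage", that others show no trend, and that others show a nonsignificant reduction.

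**The concern.** The baseline and the effect size refer to different outcomes. Stillbirths are added to raise the control rate, and a risk ratio estimated for birth before 37 weeks is then applied to them as well. There are two simple ways to read the 2.7%, and neither gives 24% v 15%.

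- If the stillbirths are extra to the 20.9%, the risk ratio was not estimated for them, and section 4.5.2 offers only mixed, non-significant results.
- If preterm stillbirths are already counted among deliveries before 37 weeks (the local 18.1% is not limited to live births), adding the full 2.7% counts them twice and the control rate is too high.

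The plan combines the higher baseline of the first reading with the undiluted risk ratio of the second. At stake is how a null result is read: it would be judged against a power figure that the protocol's own components do not support without a further, unstated assumption.

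**Working it through.** **Inputs.** Preterm rate 20.9% and stillbirth rate 2.7% (section 7.9.2); risk ratio 0.62 (section 7.9.3); two-sided Fisher's exact test at 0.05, 325 per arm, 400 enrolled per arm, loss up to 15% with half of that expected (section 7.9.4). Evaluable per arm: 400 × 0.85 = 340 at the loss allowance; 400 × 0.925 = 370 at the expected loss.

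**Method.** Exact power is the sum of Bin(x₁; n, p₁) × Bin(x₂; n, p₂) over all pairs (x₁, x₂) whose two-sided Fisher p-value is at most 0.05.

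**Plan's own figure.** 24% v 15% at 325 per arm gives 80.3%, so the stated size reproduces. At 340 it is 82.2%.

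**Rounding.** Unrounded, 23.6% v 0.236 × 0.62 = 14.6% gives 80.7% at 325. Rounding both rates is immaterial and slightly lowers power.

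**Scenario 1: stillbirths extra and unaffected.** p₁ = 0.209 + 0.027 = 0.236; p₂ = 0.209 × 0.62 + 0.027 = 0.1566; composite RR = 0.1566/0.236 = 0.66.

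**Scenario 2: no term stillbirths, all preterm ones already in the 20.9%.** p₁ = 0.209; p₂ = 0.209 × 0.62 = 0.1296; RR = 0.62.

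**Partial overlap (half of stillbirths at term, an assumed share).** p₁ = 0.209 + 0.0135 = 0.2225; p₂ = 0.209 × 0.62 + 0.0135 = 0.1431; RR = 0.64.

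| Fisher power, evaluable per arm | 325 | 340 | 370 | 400 |
|---|---|---|---|---|
| Plan: 24% v 15% | 80.3% | 82.2% | 85.5% | 88.2% |
| Scenario 1: 23.6% v 15.7% | 69.2% | 71.3% | 75.3% | 78.7% |
| Half overlap: 22.3% v 14.3% | 71.7% | 73.6% | 77.6% | 80.8% |
| Scenario 2: 20.9% v 13.0% | 74.4% | 76.3% | 80.0% | 83.2% |

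Scenario 1 needs about 414 evaluable per arm for 80%.

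**Planned test.** Section 7.9.6 compares log risks by a Z-statistic. Ignoring censoring, SE = √[(1−p₁)/(n p₁) + (1−p₂)/(n p₂)] and power = Φ(|ln(p₂/p₁)|/SE − 1.96). For scenario 1 at 340, SE = √(0.00952 + 0.01584) = 0.159, 0.410/0.159 = 2.58, and power is 73.1%. Scenario 2 gives 77.6%. At 370 the two values are 76.6% and 81.0%. The gain over Fisher is about 1–2 points.

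**Limits of the bracket.** Scenarios 1 and 2 enclose partial overlap only if 0.62 covers all deliveries before 37 weeks and no term stillbirths. If all stillbirths lie within the 20.9% and are unaffected, p₂ = 0.182 × 0.62 + 0.027 = 14.0% and power at 340 falls to 62.7%. If all 2.7% are extra but the preterm ones are also cut by 38%, power at 340 is about 77–80%, depending on the assumed term share.

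**The case against.** **The plan postulates an effect on the composite, and its arithmetic is right.** This stands. A reader might infer a miscalculation, or that rounding up to 24% inflated the power; the reproduced 80.3% and the unrounded 80.7% rule out both. The question is whether the assumption is supported.

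**Power of 71–76% is tied to the maximum loss.** This also stands. Section 7.9.4 expects about half of 15%, and at 370 per arm scenario 2 reaches 80%. The documents therefore do not support saying outright that the trial has 71–76% power.

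**Scenario 1 is an extreme.** It needs no overlap and no effect on any stillbirth. Section 4.5.2 shows uncertainty in both directions and does not establish a zero effect. That is fair, but uncertainty is not support for a 38% reduction either.

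**The baseline is deliberately cautious.** Section 7.9.2 averages the local 18.1% with a model estimate that the authors think too low, and adds nothing for ART. If 20.9% is scaled by 18.1/15.5, the preterm rate is 24.4%. Even scenario 1 then gives 27.1% v 17.8% and just over 80% power at 340. This could offset the whole shortfall, but it is a separate assumption that the stated power does not invoke.

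**The enrolment margin covers uncertainty.** Only in part: 325/0.85 rounds up to 383, which leaves 17 women per arm beyond the full loss allowance. Section 7.9.4 refers to Figure 2 for other combinations; it is not reproduced in the text reviewed here, so it could not be checked.

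**Conclusion.** The point holds as a mismatch between the baseline and the effect size, of moderate weight. The protocol neither justifies 0.62 for stillbirth nor says how far the 2.7% overlaps with the 20.9%. Under the two bracketing scenarios, Fisher power is 69–74% at 325 per arm, where the 80% is claimed, 71–76% at the 15% loss allowance, 75–80% at the expected loss, and 79–83% with no loss.

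These figures rest on the protocol's 20.9%, 2.7% and 0.62, and on 0.62 covering all deliveries before 37 weeks but no term stillbirths. The overlap is not given in the document. A reader might conclude that the trial is underpowered whatever happens. The protocol does not support that, because one scenario reaches 80% at the expected loss and the true baseline may be higher than assumed.

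**What to change.** Revise sections 7.9.2 to 7.9.4:

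1. Build the control rate from non-overlapping parts, live preterm birth plus stillbirth, and say whether the preterm sources include stillbirths.
2. Apply 0.62 only to the part for which it was estimated, or justify its use for stillbirth.
3. Restate power with its conditions: about 71–76% at the 15% loss allowance and about 75–80% at the expected loss. Alternatively, state the composite risk ratio detectable with 80% power, which at 340 evaluable per arm is about 0.63 for a control rate of 24% and about 0.61 for 21%.
4. Say that the control rate may be conservative and that this could offset the shortfall.

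The cost is a text change and a less favourable stated power. The 800 women, the endpoint and the analysis stay as they are.
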